## Abstract

**Background:**

Prevalence of cardiovascular risk factors is unevenly distributed among occupational groups. The working environment, as well as lifestyle and socioeconomic status contribute to the disparity and variation in prevalence of these risk factors. High physical work demands have been shown to increase the risk for cardiovascular disease and mortality, contrary to leisure time physical activity. High physical work demands in combination with a low cardiorespiratory fitness infer a high relative workload and an excessive risk for cardiovascular mortality. Therefore, the aim of this study is to examine whether a worksite aerobic exercise intervention will reduce the relative workload and cardiovascular risk factors by an increased cardiorespiratory fitness.

**Methods/design:**

A cluster-randomized controlled trial is performed to evaluate the effect of the worksite aerobic exercise intervention on cardiorespiratory fitness and cardiovascular risk factors among cleaners. Cleaners are eligible if they are employed ≥ 20 hours/week, at one of the enrolled companies. In the randomization, strata are formed according to the manager the participant reports to. The clusters will be balanced on the following criteria: Geographical work location, gender, age and seniority. Cleaners are randomized to either I) a reference group, receiving lectures concerning healthy living, or II) an intervention group, performing worksite aerobic exercise “60 min per week”. Data collection will be conducted at baseline, four months and 12 months after baseline, at the worksite during working hours. The data collection will consist of a questionnaire-based interview, physiological testing of health and capacity-related measures, and objective diurnal measures of heart rate, physical activity and blood pressure. Primary outcome is cardiorespiratory fitness.

**Discussion:**

Information is lacking about whether an improved cardiorespiratory fitness will affect the cardiovascular health, and additionally decrease the objectively measured relative workload, in a population with high physical work demands. Previous intervention studies have lacked robust objective measurements of the relative workload and physical work demands. This study will monitor the relative workload and general physical activity before, during after the intervention, and contribute to the understanding of the previously observed opposing effects on cardiovascular health and mortality from occupational and leisure time physical activity.

**Trial registration:**

The study is registered as ISRCTN86682076.

## Background

The prevalence of precursors of cardiovascular diseases such as hypertension and obesity is unevenly distributed across occupational groups and ethnicities [1-4]. This distribution in prevalence of cardiovascular risk factors reflects variation in lifestyle behaviour and socioeconomic status [1-4]. Factors within the working environment, as well as lifestyle behaviour and socioeconomic status contribute to the disparity and variation in the prevalence of these diseases between occupational groups [5-7]. Factors in the working environment receiving most attention in relation to cardiovascular diseases are psychosocial stressors, shift work and occupational noise [8]. More recently, high physical work demands have been shown to increase the risk of cardiovascular disease [9] and mortality [10]. This may be explained by upper limb activity increases heart rate and blood pressure [11] at the same absolute intensity as during lower limb activity. Additionally will the relatively higher aerobic workload for performing an absolute work task with low, compared to high, cardiorespiratory fitness, Figure1, [12] will contribute to an excessive stress on the arterial wall and thereby it could constitute a cardiovascular risk. One potential explanation of this is the inflammation and cholesterol deposition in arterial endothelia, decreasing the lumen-diameter and the level of contractility of arterial layer of smooth muscle, giving rise eventually to arteriosclerosis and hypertension [13]. 

**Figure 1 F1:**

Conception of the relative workload.

This proposed physiological mechanism is supported by the finding that a combination of high physical work demands and low cardiorespiratory fitness confers excessive risk for cardiovascular disease mortality [14,15], hypothetically by the increased relative aerobic workload, Figure1. This may be explained by the higher relative aerobic workload and excessive wall-stress on arterial endothelia, experienced by an employee with low, compared to an employee with high, cardiorespiratory fitness [16].

In line with this, the international recommendations for aerobic workload are based on the physical work demands relative to the cardiorespiratory fitness of the employee [17-19]. The present international recommendation for aerobic workload is a maximum average intensity of 30 % of maximal oxygen consumption during an 8 hour working day [17-19].

Strategies to reduce the risk of cardiovascular disease in occupational groups with high physical work demands have among others included implementation of ergonomic adjustments for reducing the aerobic workload [20]. However, these adjustments have not been successful in reducing the aerobic workload [20,21]. Another strategy for reducing the relative aerobic workload is to implement initiatives aiming at improved cardiorespiratory fitness, [15,22]. In theory, an increased cardiorespiratory fitness will reduce the relative aerobic workload, Figure1[23]. However, high quality studies evaluating the effects on aerobic workload of intensive aerobic exercise and increased cardiorespiratory fitness are lacking [22]. 

**Figure 2 F2:**
[figure not shown]
**Randomization procedure, multilevel design.** The clusters are randomised into either reference (R) or intervention group (I). Stratum (A, B, C) are defined by the manager the participant reports to. Clusters are formed from geographical work location, gender, age and seniority. Clusters are paired according to number of participants, gender, age and seniority.

Cleaners constitute an occupational group with high prevalence of hypertension, obesity and cardiovascular disease [7,24], which is in agreement with their well-documented high physical work demands and low cardiorespiratory fitness [12,25]. Several initiatives for decreasing the physical work demands among cleaners have been evaluated [23,25], but with no reports about significant effects on either the workload or cardiovascular health [7]. Furthermore, no previous study has investigated the effects on aerobic workload and cardiovascular risk factors following an intervention with intensive aerobic exercise, aiming at increased cardiorespiratory fitness among cleaners.

Therefore, the main aim of this study is to examine whether a worksite aerobic exercise intervention among cleaners will reduce the relative workload and cardiovascular risk factors by increasing cardiorespiratory fitness. The main hypotheses of the study are that the intervention will 1) increase cardiorespiratory fitness, and 2) decrease diurnal ambulatory blood pressure.

## Methods and design

### Study design

A cluster-randomized controlled trial will be conducted to evaluate the effect of a worksite intervention on cardiorespiratory fitness, relative aerobic workload and cardiovascular risk factors among cleaners. The cleaners consenting to participate in the trial will be randomized to either I) a reference group receiving 5 lectures about healthy living during the one year intervention period, or II) an intervention group performing worksite aerobic exercise of 60 minutes duration per week.

Outcomes will be measured at baseline, 4 months and 12 months after baseline. The study has been approved by the Danish data protection agency and the Ethics Committee for the regional capital in Denmark (journal number H-2-2011-116) and will be conducted in accordance with the Helsinki declaration. Prior to written consent to participate, information about the general aims of the study will be given to participants. The study is registered as ISRCTN86682076 in the current controlled trials.

The study is divided into two intervention phases with different aims. The aim of the first phase is to evaluate the efficacy of the intervention on cardiorespiratory fitness and cardiovascular risk factors. The aim of the second phase is to evaluate the effectiveness of the intervention on maintenance of coherence and cardiorespiratory fitness.

### Power calculation

The power calculation shows that an expected increase of 4 % in cardiorespiratory fitness will take 52 participants in each of the two intervention groups to show significance at a level of 0.05 %. The expected increase in cardiorespiratory fitness is based on an expected drop out of participants of 30 %. It is planned to recruit 52 participants for each intervention group, to attain this participation, we plan to present the study for 130 cleaners, according to the assumption of a 40 % recruitment to the study.

Earlier studies show an increased cardiorespiratory fitness in physical activity interventions at the worksite of 7 – 10 % [26,27]. This study will be analyzed according to the intention to treat and therefore are the expected drop out included in the expected increasement of cardiorespiratory fitness. The expected drop out will decrease the average increased cardiorespiratory fitness, explained by the relative smaller increasement in cardiorespiratory fitness of the drop outs than the participants following the whole intervention.

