### Randomization

The employees who volunteer to participate in the study and attend the baseline health check will be randomized to either a reference or an intervention group. The randomization will be performed at cluster-level for prevention of contamination between participating colleagues, Figure2. Clusters are set within strata. Each stratum is formed according to which manager the participant reports to. The clusters will be balanced on geographical work location, gender, age and seniority. Within each stratum, the clusters will be paired to minimize imbalance across several strata. Clusters will be paired according to number of participants, gender, age and seniority. Strata will be named alphabetically, and clusters will be named consecutively within each stratum. The randomization will be carried out by researchers blinded to the identity of the strata and clusters. All paired clusters assigned to the specific stratum will be drawn from an opaque, tossed bag and will be alternately allocated to either reference or intervention group, depending of the flip of a coin. Tails will decide allocation of the first of the two drawn paired clusters to the reference group and heads to the intervention group. The second of the two drawn paired clusters will be allocated to the opposite group to the first.

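### The power paragraph gives 52 per group with no stated allowance for clustering or for missing step tests, and its recruitment figures yield 52 in total

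*Protocol article*

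**What the plan says.** The Power calculation section states that "an expected increase of 4 % in cardiorespiratory fitness will take 52 participants in each of the two intervention groups to show significance", and then: "It is planned to recruit 52 participants for each intervention group". To reach that number, the study is to be presented to 130 cleaners, with 40 % uptake assumed.

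On drop-out, the same section says "The expected increase in cardiorespiratory fitness is based on an expected drop out of participants of 30" %. It explains that under intention to treat "therefore are the expected drop out included in the expected increasement of cardiorespiratory fitness", because people who drop out gain less fitness than those who complete. The undiluted benchmark is: "Earlier studies show an increased cardiorespiratory fitness in physical activity interventions at the worksite of 7 – 10" %.

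On design, the Randomization section says "The randomization will be performed at cluster-level for prevention of contamination between participating colleagues", with clusters paired inside manager strata. The Statistical analysis section plans multilevel analyses of the primary and secondary outcomes.

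**The concern.** The paragraph presents a finished calculation. It explains its effect size, its treatment of drop-out and its uptake assumption, but does not mention the feature that defines the design. Colleagues in one cluster tend to resemble each other, so a cluster-randomized comparison usually carries less information than the same number of individually randomized people. If 52 was computed for individuals, the trial has less power for a 4 % increase than readers will assume, and a null primary result could be misread as evidence of no effect.

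Two further gaps sit in the same paragraph. Lowering the expected effect accounts for people who stop exercising but still do the step test. It does not account for people with no test at 4 or 12 months. The recruitment sentence also does not lead to 52 per group.

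**Working it through.** **Inputs from the article:** 52 per group needed; 52 per group to be recruited; effect 4 %; drop-out 30 %; earlier effects 7–10 %; 130 cleaners approached; 40 % uptake.

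**Inputs not given, so assumed:** power 80 %; two-sided 5 % (the section prints "to show significance at a level of 0.05" %, which I take to mean 0.05); mean cluster size m = 4 to 13; ICC = 0.01 to 0.10; 52 computed as for individual randomization.

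**1. Can 52 be reproduced?** No, because neither SD nor power is stated. Solving backwards with the normal approximation, d = √(2/52) × (1.960 + 0.842) = 0.549. A 4 % increase then implies an SD of 4/0.549 = 7.28 % of the mean. For 90 % power the values are d = 0.636 and SD 6.29 %. Exact t calculation gives d = 0.555 for 80 % power. The 52 can be neither confirmed nor refuted.

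**2. Clustering.** Design effect DE = 1 + (m − 1) × ICC; effective n = 52/DE; detectable increase at 80 % power ≈ 4 % × √DE; number needed per group = 52 × DE, rounded up. Power is from the two-sample t test with d = 0.555 at the effective n.

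| m | ICC | DE | Effective n per group | Power for 4 % | Detectable increase | Needed per group |
|---|---|---|---|---|---|---|
| 4 | 0.01 | 1.03 | 50.5 | 79 % | 4.1 % | 54 |
| 8 | 0.05 | 1.35 | 38.5 | 67 % | 4.6 % | 71 |
| 13 | 0.10 | 2.20 | 23.6 | 46 % | 5.9 % | 115 |

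The normal approximation gives 79 %, 67 % and 47 %. The table takes no credit for pairing or baseline adjustment. It also makes no deduction for the few cluster-level degrees of freedom (52/13 = 4 clusters per group in the last row).

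**3. Drop-out as dilution.** If 30 % drop out and gain nothing, the average gain is 0.7 × 7 % = 4.9 % to 0.7 × 10 % = 7.0 %. The planned 4 % lies below this range, so stopping exercise is already absorbed.

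**4. Missing tests.** Needed minus recruited is 52 − 52 = 0 per group, so no margin is stated for participants without a follow-up step test. The article gives no expected rate of missing tests, so I put no figure on the loss.

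**5. Recruitment.** 130 × 0.40 = 52 in total, or 26 per group. The plan needs 2 × 52 = 104, and 104/0.40 = 260 cleaners. With 26 per group, power under the step 1 assumptions would be about 50 % even without clustering.

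**The case against.** - **A design effect may already be inside the 52.** SD, power and method are not printed, so this cannot be excluded. A reader might infer that the effective size is certainly below 52 per group; the article does not support that certainty. What stands is that no allowance is stated.
- **The loss may be small, or partly recovered.** At m = 4 and ICC 0.01 it is negligible. Pairing on size, gender, age and seniority, and a baseline fitness measurement, could recover some precision. The 4 % may also be cautious: 4.9 % from step 3 exceeds the 4.6 % detectable in the middle row. It does not exceed the 5.9 % in the last row, and the paragraph does not offer that margin as cover for clustering.
- **Drop-out is accounted for.** A reader might infer that the trial ignores its own 30 % drop-out. It does not; the diluted effect agrees with its own figures. Nor should one take 30 % as unmeasured (52 × 0.7 = 36.4 per group, about 65 % power) while keeping the 4 %. That uses the same 30 % twice, and the article gives no 30 % missing rate. Only the narrower point stands: dilution presupposes that drop-outs are tested.
- **Cluster composition.** The Figure 2 legend says "Clusters are formed from geographical work location, gender, age and seniority", which might suggest clusters alike in gender and age and hence a high ICC. The abstract and the Randomization section instead speak of balancing clusters on these factors, so the wording cannot carry that argument.
- **The 130 might mean 130 per group.** That would give 104, but the text does not say so, and people are approached before they are randomized.
- **It is a condensed article.** The full protocol may hold the ICC and cluster count. However, the article states a complete calculation and a conclusion from it, and these should fit the design it describes.

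**Conclusion.** The point holds in a limited form. The power paragraph claims that 52 per group suffice for a 4 % increase and states no allowance for clustering, although the trial randomizes clusters and plans a multilevel analysis. It also states no separate allowance for missing step tests. If 52 was derived for individuals at 80 % power and two-sided 5 %, true power lies between about 79 % and 46 % over the assumed range, and the detectable increase between about 4.1 % and 5.9 %. These sizes depend on an ICC and a cluster size that the article does not give.

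The recruitment mismatch depends on none of these assumptions: as written, 130 cleaners at 40 % uptake supply half of the planned 104.

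**What to change.** Rewrite the Power calculation paragraph for the cluster design:

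- State the SD, the power, the sidedness and the significance level, correcting the printed percentage if 0.05 is meant.
- State the number and mean size of clusters, the assumed ICC with its basis, and the design effect 1 + (m − 1) × ICC. If a design effect is already inside the 52, say so and show it.
- Give the expected number with a follow-up step test, kept separate from the dilution for people who stop exercising.
- State the increase that the planned 52 per group can detect, with any credit taken for pairing or baseline adjustment.
- Reconcile recruitment: either about 260 cleaners are approached for 104 participants at 40 % uptake, or the uptake or target changes.

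The cost is one paragraph and a probably less favourable detectable effect. Restating power needs no enrolment beyond the planned 104. Reaching 104 may mean approaching more cleaners than the 130 stated.

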### Outcomes

The primary outcome of this trial is cardiorespiratory fitness (mlO_2_* min^-1^ * kg^-1^), Figure3. Secondary outcomes are diurnal heart rate, physical activity, body position and ambulatory blood pressure, relative aerobic workload (percent of heart rate reserve (%HRR)) self-rated work productivity, rate of perceived exertion (RPE) during work, intensity and number of regions with self-rated musculoskeletal pain, high sensitive C-reactive protein (hsCRP), high density lipoprotein (HDL), glycated haemoglobin (HbA1c), self-rated need for recovery and participation in intervention.

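### The only significance level in the protocol is printed as 0.05 % (alpha = 0.0005), almost certainly a unit error for 0.05 (5 %)

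*Protocol article*

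**What the plan says.** All figures are in the Power calculation section of the protocol article.

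- **Effect:** "an expected increase of 4 % in cardiorespiratory fitness".
- **Size:** this "will take 52 participants in each of the two intervention groups", and the recruitment plan repeats the number: "It is planned to recruit 52 participants for each intervention group".
- **Level:** the number is the one required "to show significance at a level of 0.05", with a percent sign directly after the figure.
- **Dropout:** "The expected increase in cardiorespiratory fitness is based on an expected drop out of participants of 30" %, so dropout is absorbed in the effect and does not inflate the number recruited.

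The Outcomes section names the endpoint: "The primary outcome of this trial is cardiorespiratory fitness". The Statistical analysis section announces multilevel analyses at the measurement times and gives no significance level. The article states no SD, power or sidedness.

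**The concern.** A level of 0.05 % is alpha = 0.0005. Nothing in the article explains why a trial of this kind would plan at that level, while 0.05 written as a proportion is the usual choice. The likely explanation is that a percent sign was added to a proportion.

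The figure is an input to the sample size and the only error rate the published plan gives for its primary outcome. If the primary result has a p-value between 0.0005 and 0.05, it misses the printed level and meets the conventional one. Deciding after the data are seen which level was meant invites a dispute that one corrected number would prevent.

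**Working it through.** **1. The printed level.** 0.05 % = 0.05/100 = 0.0005, and 0.05/0.0005 = 100.

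**2. Could 0.0005 be deliberate?** The Background names two main hypotheses, and there are two follow-up times (4 and 12 months). A Bonferroni split over those four tests would give 0.05/4 = 0.0125. Reaching 0.0005 that way takes 0.05/0.0005 = 100 tests. The article describes no multiplicity correction and no interim analysis.

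**3. Can the plan's 52 be reproduced?** Inputs from the Power calculation section are a difference of 4 (taken here as percentage points between groups), n = 52 per group and 1:1 allocation. SD, power and sidedness are not given. For a comparison of two means between individuals, by the normal approximation,

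n = 2 (z_alpha + z_power)² (SD/4)², so SD = 4 / [(z_alpha + z_power) √(2/52)], with √(2/52) = 0.196.

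With two-sided z_alpha = 1.960 at 0.05 and 3.481 at 0.0005, and z_power = 0.842 (80 %) or 1.282 (90 %), the SD that yields 52 is:

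| Two-sided alpha | Power 80 % | Power 90 % |
|---|---|---|
| 0.05 | 7.28 | 6.29 |
| 0.0005 | 4.72 | 4.28 |

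The t-distribution gives 7.2 and 6.2 in the first row, and 4.6 and 4.2 in the second. Thus 52 fits either level, depending on an SD that is not stated. It can be neither reproduced nor refuted, and it does not reveal which alpha was used.

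**4. What is at stake if 52 was derived at two-sided 5 %.** Keep the SD from the first row and test at 0.0005. By the normal approximation, power = Φ(z_0.05 + z_power − z_0.0005):

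- 80 % case: Φ(1.960 + 0.842 − 3.481) = Φ(−0.679) = 25 %.
- 90 % case: Φ(1.960 + 1.282 − 3.481) = Φ(−0.239) = 41 %.

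The noncentral t, which is more exact at this size, gives 23 % and 38 %. The number per group that restores the assumed power is about 125 (80 %) or 114 (90 %) by the t-test, and 124 or 113 by the normal approximation. If 52 had instead been derived one-sided, the normal approximation gives 21 % and 36 % power at one-sided 0.0005.

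**5. What is at stake if the derivation is left open.** Two-sided power at n = 52 and difference 4, normal approximation:

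| SD (percentage points) | alpha 0.05 | alpha 0.0005 |
|---|---|---|
| 4 | 99.9 % | 94.7 % |
| 4.5 | 99.5 % | 85.4 % |
| 5 | 98.3 % | 72.5 % |
| 6 | 92.5 % | 46.8 % |
| 7 | 83.0 % | 28.5 % |
| 8 | 72.2 % | 17.6 % |
| 10 | 53.2 % | 7.5 % |

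The loss ranges from slight to severe with the SD. All these figures treat participants as independent. The trial randomizes clusters, which would lower power at either level.

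**The case against.** The strongest reply is that this is a misprint in a planning input. The Statistical analysis section sets no test threshold, most readers would take the figure as 5 %, and the recruitment target and design do not change. It is also fair that an article may leave the SD and power to a fuller document. Their absence is therefore not the point here and matters only because it prevents a check.

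Much of this stands. A reader might infer that 52 per group cannot detect the planned effect at the printed level. The article does not support that: with an SD of about 4.7 or less (about 4.6 by the t-test), 52 per group reaches 80 % power even at 0.0005. A reader might also infer that the trial would usually be declared negative when the effect is real. That follows only if 52 was calculated at 5 %, and only if a level printed in the power section is applied as the test rule. The 23 % and 38 % come from that assumption and do not test the printed figures.

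The reply does not make the printed figure right. The article commits itself to a level, gives it only once, and offers no reason for so strict a value.

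**Conclusion.** The significance level is wrong as printed, or at the least unexplained. It differs from convention by a factor of 100 and is almost certainly a unit error for 0.05 (5 %).

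The effect on power depends on how 52 was derived. On the assumption of two-sided 5 % with 80 % or 90 % power, individual-level comparison and no clustering, the printed level would leave about 23 % or 38 %. On the alternative assumption that 0.0005 was the planning level, there is no shortfall from this source. The article cannot decide between them. Confidence is high that the figure needs correction. No failure of the sample size has been shown on this point.

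**What to change.** Go back to the calculation, confirm the level actually used, and print it in place of 0.05 %. If it was 5 %, write 0.05 or 5 %. State whether it is one-sided or two-sided, since the article does not say and it should not be presumed. Do this before the data are analysed, so that the published threshold for the primary comparison is unambiguous.

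Do not add SDs solved backwards from 52. The values in the working depend on assumed power and ignore clustering, so printing them would supply a justification after the fact. If the original SD and power are on record, those can be given beside the level.

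The cost is one corrected number and one added word. If the level proves to have been 5 %, nothing changes in recruitment, design or analysis.

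### The number of cleaners to be approached (130) does not match the recruitment target: 52 per group at 40 % recruitment needs 260, and 130 yields 52 in total.

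*Protocol article*

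**What the plan says.** All the figures stand in the Power calculation section of the protocol article.

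- **Requirement.** An expected 4 % increase in cardiorespiratory fitness "will take 52 participants in each of the two intervention groups".
- **Recruitment target.** The same number appears as a target: "It is planned to recruit 52 participants for each intervention group". Two groups of 52 make 104.
- **Means of reaching it.** The same sentence goes on: "we plan to present the study for 130 cleaners, according to the assumption of a 40 % recruitment to the study".
- **Dropout.** A 30 % dropout is expected. The section says it is already reflected in the expected increase, which is set below the 7 to 10 % seen in earlier worksite studies. It is not used to raise the sample size.

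The Randomization section gives the order of events: "The employees who volunteer to participate in the study and attend the baseline health check will be randomized" to one of the two groups. The Recruitment section says that all employees of an enrolled company were invited to an information meeting. Approach and recruitment therefore come before allocation, and one pool of cleaners supplies both groups.

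**The concern.** The number to approach is the link between the sample size and the companies that have to be enrolled. The plan offers 130 as the way to attain 52 per group, but at its own 40 % rate 130 gives 52 people altogether. The target, the recruitment rate and the number to approach cannot all be right if 130 is the total, which is how the sentence reads.

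If the study team planned the number of companies and information meetings around 130, the trial could enrol half its stated sample. Power for the primary outcome, cardiorespiratory fitness, would then be well below whatever the sample size calculation assumed.

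**Working it through.** **Inputs from the Power calculation section:** 52 per group; 2 groups; 130 cleaners approached; 40 % recruitment; 30 % dropout; 4 % expected increase.

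**1. Reproducing the printed figure.** Number to approach = participants needed / recruitment rate.

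- One group: 52 / 0.40 = 130. This matches the printed figure exactly.
- Both groups: (2 × 52) / 0.40 = 104 / 0.40 = 260. This is twice the printed figure.

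**2. What 130 delivers.** 130 × 0.40 = 52 in total, and 52 / 2 = 26 per group. Recruiting 104 from 130 would need 104 / 130 = 80 %, double the assumed rate.

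**3. Could dropout account for 130?**

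- Raising the total for 30 % dropout: 104 / 0.70 = 148.6, so 149; 149 / 0.40 = 372.5, so 373.
- Counting completers only: 104 × 0.70 = 72.8; 72.8 / 0.40 = 182.

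Neither gives 130. No route tried that covers both groups gives 130.

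**4. Consequence if invitations ended at 130.** The article states neither the planned power nor the SD, and prints the significance level as 0.05 %. I assume a two-sided 5 % level and a planned power of 80 % or 90 %. The comparison is a simple two-group comparison of means between individuals, without clustering.

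Standardised effect implied by 52 per group: d = (1.960 + z_power) × √(2/52), with √(2/52) = 0.196.

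Power at 26 per group: Φ(d × √(26/2) − 1.960), with √(26/2) = 3.606.

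| Planned power | d | SD implied by a 4 % effect | d × 3.606 − 1.960 | Power at 26 per group |
|---|---|---|---|---|
| 80 % | (1.960 + 0.842) × 0.196 = 0.549 | 4 / 0.549 = 7.3 % | 0.02 | 51 % |
| 90 % | (1.960 + 1.282) × 0.196 = 0.636 | 4 / 0.636 = 6.3 % | 0.33 | 63 % |

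With the t distribution in place of the normal, the results are 50 % and 62 %. If the significance level is taken literally as 0.05 % (0.0005), the same normal calculation gives 34 % and 46 %.

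**5. Detectable effect at half the sample.** The detectable difference varies with 1/√n, so halving n multiplies it by √2 = 1.41. This factor does not depend on the SD or the planned power. It does assume that the clustering penalty stays the same, for example half as many clusters of the same size. With the same number of clusters at half the size, the factor would be smaller if there is any positive intracluster correlation.

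**The case against.** **The 130 may be meant per group.** The sentence opens with a per-group target, and 52 / 0.40 is exactly 130, so the division is correct for the quantity just named. The authors may simply have left out the words for per group. This explains how the figure arose, but it does not make the text right. The sentence does not say per group, and nobody belongs to a group when approached, because allocation follows consent and the baseline health check. On this reading too, the number to approach is 260 and the text has to say so.

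**The 130 is not a cap.** A reader might infer that the trial will enrol only half its sample. The documents do not support that. The target of 52 per group is stated twice, and 130 is only the planned means of reaching it. The Recruitment section describes inviting all employees. The Study population section requires more than 50 cleaners at each company, and the Strengths and limitations section speaks of several companies. Nothing says that invitations stop at 130. The number of companies and employees is not given either, so the documents do not show that 260 would be reached. This objection stands: the loss is conditional.

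**Loss of power is not inability.** A reader might also infer that the trial could not show the 4 % increase. Power of about 50 to 62 % is poor, but it is not zero, and the figures rest on assumptions that the article does not state. This objection also stands.

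**Conclusion.** The recruitment figures contradict each other. A target of 104 at 40 % recruitment needs 260 cleaners approached. The stated 130 supplies one group of 52, or 26 per group when shared between two. This conclusion uses only the plan's own numbers and needs no assumption about power, SD or clustering. The per-group reading changes the explanation but not the need for a correction.

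The consequence is conditional. If invitations ended at 130, the trial would enrol half its stated sample. On the assumption that 52 per group gives 80 to 90 % power at a two-sided 5 % level, power for the same 4 % increase would be about 50 to 62 %, before any allowance for clustering.

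It is tempting to turn the factor of 1.41 into a new detectable increase (4 % × 1.41 = 5.7 %) and write that into the protocol. The documents do not support this: the article gives no SD, power or intracluster correlation, so 5.7 % only shows the direction and rough scale.

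**What to change.** Replace 130 with 260 in total (104 / 0.40), or write 130 per group, 260 in total, if that was the intent. Then check that the enrolled companies together employ at least 260 eligible cleaners.

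If only 130 can be approached, give the expected sample as 52 in total (26 per group). Recompute the detectable increase from the trial's own SD, planned power and clustering allowance. Other things equal, it will be about 1.4 times the planned 4 %.

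The change to the text is one figure. The practical cost is either a larger invitation effort, possibly with more companies, or a less favourable detectable effect. The allocation method, outcome and analysis stay as they are.
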